## Abstract

**Background:**

Propofol sedation in patients with Obstructive Sleep Apnea (OSA) frequently induces hypoxemia, posing significant clinical risks. Esketamine, an N-Methyl-D-Aspartate (NMDA) receptor antagonist, may reduce propofol requirements while preserving respiratory stability, but its efficacy in OSA patients remains unproven. At the studied dose (0.25 mg/kg), esketamine’s potential side effects (transient hypertension) are expected to be mild and self-limited. Therefore, we aimed to test whether low-dose esketamine (0.25 mg/kg) can reduce the incidence of hypoxemia in moderate-to-high risk OSA patients during propofol-based painless gastroscopy.

**Discussion:**

This protocol rigorously evaluates esketamine’s potential to improve sedation safety in OSA patients, addressing a critical gap in peri-procedural care.

**Trial registration:**

Chinese Clinical Trial Registry (ChiCTR2500099420). Registered on March 24, 2025 (Supplementary File 2). [name] is a co-first author with the same contribution as the first author. The corresponding author is [name].

## Introduction

### Background and rationale {6a}

Gastric cancer is among the most prevalent and lethal malignancies globally [1]. Early detection through screening can improve five-year survival rates to approximately 70%, while advanced-stage disease carries a significantly poorer prognosis of about 20% survival [2, 3]. Gastroscopy serves as the gold standard for both screening and early diagnosis of gastric neoplasms. Propofol sedation, while improving patient comfort, frequently induces hypoxemia and hypotension [4], complications exacerbated in patients with moderate-to-high risk OSA (STOP-Bang score ≥ 3) [5, 6].

The pathophysiology of sedation-associated hypoxemia in these patients involves multiple factors: anatomical airway narrowing, increased thoracic negative pressure, gastroesophageal reflux, chronic pharyngitis, and excessive sedative dosing. OSA has been independently associated with hypoxemia during endoscopic procedures [7], and its prevalence in the general population ranges from 2 to 26% [8]. These findings underscore the critical importance of optimal airway management and judicious sedative selection in this vulnerable population.

The ideal sedative adjunct should simultaneously reduce propofol requirements while minimizing adverse effects on oxygenation and hemodynamics, while still maintaining excellent procedural conditions. Current alternatives present significant limitations: midazolam and opioids exacerbate respiratory and cardiovascular depression [9]; ketamine may induce psychotomimetic effects [10]; dexmedetomidine frequently causes prolonged hypotension and bradycardia [11, 12]; and intravenous lidocaine carries toxicity risks [13].

Esketamine, the S-enantiomer of ketamine, offers several pharmacological advantages as an NMDA receptor antagonist. It provides synergistic sedation and analgesia while exhibiting minimal respiratory depression [14, 15]. Clinical studies demonstrate its propofol-sparing effects and excellent safety profile during urological procedures in elderly patients [16]. At the studied dose (0.25 mg/kg), its potential side effects—including transient hypertension, tachycardia, and emergence phenomena—are typically mild and self-limited [17]. However, evidence regarding esketamine’s efficacy in preventing hypoxemia during gastroscopy in moderate-to-high risk OSA patients remains limited.

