### Outcomes and definitions {12}

Primary outcome is the hypoxemia incidence, defined as SpO_2_ < 90% for > 10 consecutive seconds during the procedure [18]. Timing begins at first SpO_2_ reading < 90% and continues until resolution.

Secondary outcomes are as follows:Severe hypoxemia incidence, defined as SpO₂ ≤ 75% for any duration or SpO₂ ≤ 90% for ≥ 60 consecutive seconds or longer during the procedure [17].Hypoxemia duration, defined as total cumulative time (seconds, mean [SD]/median [IQR]) with SpO₂ < 90% during procedure.Emergency airway intervention, defined as requiring jaw thrust maneuver, mask-assisted ventilation with procedure interruption, tracheal intubation during procedure and in PACU.Hypotension incidence defined as MAP decrease ≥ 20% compared with baseline (average of 3 pre-procedure readings) during procedure and in PACU.Involuntary body movements are defined as any limb/trunk movements requiring physical restraint or procedure interruption during the procedure.Total propofol dose defined as cumulative amount (mg, mean [SD]/median [IQR]) administered during procedure.Length of procedure (minutes, mean [SD]/median [IQR]) defined as the time quantum from gastroscope insertion to complete withdrawal.Recovery time (minutes, mean [SD]/median [IQR]) defined as the time quantum from scope removal to achieving MOAA/S score of 5 or responsive to normal voice.Clinician satisfaction measured via 10-cm VAS immediately post-procedure (0 = extremely dissatisfied, 10 = completely satisfied) after the procedure.AEs will be documented and assessed continuously during the procedure and in the PACU. Occurrence counts and severity (where applicable) will be documented in the CRFs as follows:Cough: Defined as ≥2 consecutive coughs during the procedure or in the PACU; assessed by direct observation and recorded as presence/absence.Hiccups: Defined as ≥2 episodes within 1 minute; recorded as presence/absence during the procedure or in the PACU.Nausea/vomiting: Graded on a 3-point severity scale (1=mild/nausea only, 2=moderate/transient vomiting, 3=severe/prolonged vomiting) and assessed both during the procedure and in the PACU.Reflux/aspiration: Defined as visible gastric content in the oropharynx or airway; recorded as presence/absence during the procedure.Laryngospasm: Defined as complete airway obstruction with no airflow despite respiratory effort; assessed by auscultation and waveform capnography, and recorded as presence/absence during the procedure.

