## Data collection and management

### Plans for assessment and collection of outcomes {18a}

All outcomes will be systematically assessed, collected, and recorded on CRFs by blinded assessors across three phases: baseline demographics (age, sex, BMI), clinical characteristics (ASA status, STOP-Bang score, Difficulty in mask ventilation [DMV] risk factors), and room-air SpO_2_ will be collected pre-procedure; continuous vital signs (HR/SpO₂/NBP recorded every 30 s), propofol requirements, hypoxemia episodes (SpO_2_ < 90% > 10 s), procedure/recovery times, and adverse events (graded by blinded assessors) collected intraprocedure; Satisfaction (10-cm VAS), PACU recovery metrics (MOAA/S = 5 time), and AEs (graded 1–3 for severity/causality) collected post-procedure.

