### Adverse event reporting and harms {22}

All predefined sedation-related AEs (hypoxemia, hypotension) will be recorded in CRFs with severity grading (1–3), assessed for causality (Definite/Probable/Possible), and reported to IRB within 48 h (24 h for SAEs). Any participant experiencing trial-related adverse events/harms will receive immediate medical management, free follow-up care until resolution of symptoms, referral to appropriate specialists if needed, and some compensation according to hospital Compensation Policy.

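### None of the three esketamine side effects named in the rationale has an incidence definition, and emergence phenomena have no systematic assessment in the text shown

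*Protocol article*

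**What the plan says.** Background and rationale {6a} describes esketamine's potential side effects at 0.25 mg/kg, "including transient hypertension, tachycardia, and emergence phenomena", and calls them typically mild. The abstract repeats one of them: "potential side effects (transient hypertension) are expected to be mild and self-limited".

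Outcomes and definitions {12} has a single haemodynamic event outcome: "Hypotension incidence defined as MAP decrease ≥ 20% compared with baseline". On adverse events it says "AEs will be documented and assessed continuously during the procedure and in the PACU", and then "Occurrence counts and severity (where applicable) will be documented in the CRFs as follows". Five items follow: cough, hiccups, nausea/vomiting, reflux/aspiration and laryngospasm. Adverse event reporting and harms {22} says "All predefined sedation-related AEs (hypoxemia, hypotension) will be recorded in CRFs".

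Three other sections bear on the point. Plans for assessment and collection of outcomes {18a} provides for "continuous vital signs (HR/SpO₂/NBP recorded every 30 s". Statistical methods {20a} compares MAP and heart rate over time by repeated measures ANOVA and tests secondary outcomes two-sided. The oversight section {5d} requires every adverse event to be graded and sent to the IRB.

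**The concern.** The protocol says which harms it expects from the test drug, and then gives event definitions to other things. It sets a frequency criterion for hiccups and a three-point scale for nausea and vomiting, so the level of detail is not the obstacle. The effects attributed to esketamine itself are absent from that list.

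The haemodynamic side is lopsided. The abstract promises haemodynamic stability as a secondary outcome, but {12} counts only falls in MAP. The rationale attributes hypotension to propofol, and the trial hopes esketamine will spare propofol. The event with an incidence definition is therefore one the drug might reduce. The pressure and heart rate rises that the drug might cause have none.

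At stake is the balance of benefit and risk. The Discussion says a positive result could change standard practice. The population includes ASA III patients and patients whose treated hypertension is within the entry limits, and blood pressure is itself a STOP-Bang item. A recommendation for such patients needs the frequency of the drug's expected harms by randomised arm, not only the frequency of hypoxemia and hypotension.

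**Working it through.** No figure in the protocol needs reproducing. The check sets each named effect against each place where it could be defined, measured or analysed.

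| Effect named in {6a} | Outcome or itemised AE in {12} | Predefined AE in {22} | Data planned | Analysis planned |
|---|---|---|---|---|
| Hypertension | No | No | Blood pressure, {18a} | MAP over time, ANOVA, {20a} |
| Tachycardia | No | No | Heart rate, {18a} | Heart rate over time, ANOVA, {20a} |
| Emergence phenomena | No | No | None specific | None |
| *For comparison:* hypotension | Yes, with threshold and baseline | Yes | Blood pressure, {18a} | Incidence by arm, plus MAP over time |

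**Count.** 0 of 3 named effects are defined as an outcome or listed AE. For 2 of 3 the underlying measurements are collected and analysed as trends. For 1 of 3 there is no specific measure at all.

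**Does the ANOVA fill the gap for the first two?** It compares mean MAP and mean heart rate between arms over time. It does not say how many patients had a marked rise. With 147 per arm, one patient with a MAP rise of 20 mmHg at a given time moves that arm's mean by 20/147 = 0.14 mmHg. As an illustration, ten such patients (10/147 = 6.8% of the arm) move it by 10 × 20/147 = 1.4 mmHg if the others are unchanged. Falls in other patients would offset even that. A frequency that matters to a clinician can leave little trace in a mean.

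**Is a rise defined anywhere?** Yes. Intervention description {11a} gives a MAP increase of at least 20 mmHg or a heart rate increase of at least 20 beats/min, but only among the reasons for giving more propofol. Under the plan such an episode shows up in the propofol total, not as an event counted by arm. Section {20b} states that no additional analyses are planned, so an incidence comparison made later would be post hoc.

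**Does any other measure reach emergence phenomena?** Recovery time in {12} ends at MOAA/S 5 or response to normal voice. That measures alertness. A patient can reach it while agitated, dysphoric or hallucinating. The remaining route is the general reporting duty in {5d}, which depends on staff noticing and naming the event without a common definition.

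**The case against.** The strongest reply is that the protocol is far from blind to these harms. Vital signs are monitored from room admission through PACU recovery, heart rate and pressure are recorded every 30 s, and the analysis is two-sided, so a rise under esketamine is as testable as a fall. All adverse events must be reported, and blinded assessors grade them. This stands. A reader might infer from the lists that the trial cannot report its drug's harms. The documents do not support that: hypertension and tachycardia can be derived from recorded data, and an emergence reaction that staff notice must be reported.

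A reader might also take the list in {12} as closed. The text does not say so. The bracket in {22} names two events and omits all five listed in {12}, so it reads more naturally as examples.

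It would likewise be too sweeping to say that only events favouring esketamine are counted. Nausea/vomiting, laryngospasm, reflux/aspiration and recovery time are recorded in both arms and could show harm.

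Nor does a rule-of-three bound measure what is lost. With no events, 3/147 = 2.0% (or 3/132 = 2.3% without the attrition allowance) is a single-arm upper limit. It applies only if nothing is observed, and it is not the comparison between arms that matters here.

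Finally, this is a condensed article. The schedule of assessments (Fig. 3) and the CRF are not shown, and either might contain an emergence item. That limits how firmly the gap can be stated. It does not explain why the detailed list in {12} leaves out the effects named in {6a}.

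**Conclusion.** The point holds in a limited form. Incidence by arm is not prespecified for any of the three side effects that the rationale names. For hypertension and tachycardia the missing piece is an event definition: the data and a trend analysis exist. For emergence phenomena the definition and the systematic assessment are both missing from the text shown.

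This does not affect the primary outcome or the validity of the randomised comparison of hypoxemia. It does weaken the harms side of the conclusion that the Discussion anticipates, and it should be corrected while recruitment is open (planned to December 31, 2026).

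The verdict assumes that the unseen CRF and Fig. 3 hold no emergence item. If they do, {12} and {22} need only be aligned with them. It also assumes that the recorded pressures allow MAP to be obtained, which the hypotension outcome already requires.

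**What to change.** Add two items to {12} and {22}.

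1. **Incidence of hypertension and of tachycardia, by arm, from the MAP and heart rate already recorded.** State one outcome threshold for each, with the baseline and observation window. The protocol offers two sources: the mirror image of its hypotension definition (a relative rise from the average of the three pre-procedure readings), or the MAP and heart rate rises already written in {11a}. Either would serve as an outcome definition only, with no change to treatment. The choice should be made without sight of results by arm, and so before the planned unblinded interim analysis is seen.
2. **Emergence reactions (agitation, hallucination, dysphoria)** as presence/absence in PACU, scored by the existing blinded assessors.

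Report each by arm with counts, the risk difference and its 95% CI.

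The cost is a protocol amendment with ethics approval and one extra CRF item. Hypertension and tachycardia can be scored for patients already enrolled, as far as their records go: {18a} states the 30-second recording for the procedure, so PACU heart rate coverage should be checked. Emergence data will exist only for patients enrolled after the amendment. The report should give that smaller denominator and should not treat earlier patients as event-free.

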#### Objectives {7}

This trial aims to determine whether intravenous low-dose esketamine (0.25 mg/kg) reduces the incidence of hypoxemia (defined as SpO_2_ < 90% for > 10 s) by ≥ 15% compared to placebo during propofol-sedated gastroscopy in patients with moderate-to-high risk OSA (STOP-Bang score ≥ 3), using a one-sided *α* = 0.025.

##### Trial design {8}

This single-center, prospective, double-blind, randomized, superiority trial will evaluate whether low-dose esketamine (0.25 mg/kg) reduces hypoxemia incidence compared to placebo during propofol-sedated gastroscopy in patients with moderate-to-high OSA risk (STOP-Bang score ≥ 3).We will enroll 294 participants, randomly allocating them in a 1:1 ratio to either Esketamine group (0.25 mg/kg esketamine + propofol) or Control group (equal-volume saline + propofol). The study duration is 21 months. Eligible patients will be screened according to inclusion/exclusion criteria, with baseline characteristics recorded in case report forms (CRFs). Continuous monitoring of vital signs will occur from gastroscopy room admission through Post-Anesthesia Care Unit (PACU) recovery, with all interventions and assessments standardized (Fig. 1).

**Fig. 1 Fig1:**
[figure not shown]
CONSORT diagram

## Methods: participants, interventions, and outcomes

### Study setting {9}

This single-center trial will be conducted at the Digestive Endoscopy Center of Beijing Friendship Hospital, Affiliated Capital Medical University.

The study workflow will include the following: (1) Participant screening—Potential participants will undergo preliminary eligibility assessment at Anesthesiology Evaluation Clinic based on predefined inclusion/exclusion criteria; (2) Eligible candidates will receive comprehensive study information, with written consent obtained by one Good Clinical Practice (GCP)-certified investigator; (3) The trial will adhere to Declaration of Helsinki principles, SPIRIT checklist (see Supplementary File 1) and Institutional Review Board (IRB). And, consent education, dedicated coordinator, withdrawal data collection will be implemented for promoting participant retention and complete follow-up. DSMB monitoring, IRB-approved, voluntary participation with no care penalties.

### Who will take informed consent? {26a}

Eligible patients will receive a verbal explanation and notice of signing the informed consent form before gastroscopy by GCP-certified investigator. Signed consent forms will be collected before randomization and stored in a locked cabinet.

### Additional consent provisions for collection and use of participant data and biological specimens {26b}

No additional consent provisions for collection and use of participant data and biological specimens in ancillary studies.

## Interventions

### Explanation for the choice of comparators {6b}

This study uses 0.9% saline placebo as the comparator for the following reasons: (1) Avoids confounding from respiratory interactions with other sedatives (opioids or benzodiazepines), which are commonly used in clinical practice but may independently affect hypoxemia. (2) Reflects real-world scenarios where propofol monotherapy is standard care for sedation in gastroscopy. Directly tests whether low-dose esketamine provides added benefit over current practice. (3) Placebo-controlled design is ethically justifiable because all patients receive propofol (standard care) as the base sedative and the trial population (STOP-Bang ≥ 3) is at high risk for hypoxemia, making detection of incremental benefits clinically meaningful.

### Intervention description {11a}

The anesthesia assessment should be completed a few days before the gastroscopy at Anesthesiology Clinic according to ASA guidelines. Once admitted to the gastroscopy room, intravenous (IV) access will be established, standardized monitoring will be continuously performed, including electrocardiogram (ECG), noninvasive blood pressure (NBP), SpO_2_, respiratory rate (RR), and waveform capnography. Then, placed in a left lateral position, investigators will deliver preoxygenation via facemask at 6 L/min.

Sedation protocol: An initial bolus of propofol (1.0–2.0 mg/kg for patients > 70 years; 1.5–2.5 mg/kg for patients < 70 years) injected. Then, esketamine 0.25 mg/kg is injected for the patients in Group E, while equal-volume saline solution is administered for Group C. Additional propofol (10–50 mg) boluses could be titrated until the palpebral reflex disappears or Modified Observer’s Assessment of Alertness/Sedation (MOAA/S) score of 2. During the procedure, additional propofol (10–50 mg) could be administered again for maintaining a MOAA/S score of 2 or addressing cough (≥ 2 consecutive coughs), grimaces (visible facial muscle contraction), involuntary body movements (limb/trunk movements requiring restraint), and hemodynamic instability (mean arterial pressure [MAP] increase ≥ 20 mmHg or heart rate [HR] increase ≥ 20 beat/min).

Emergency Airway Management: If the SpO_2_ dropped below 90% during the procedure, the airway management protocol in Fig. 2 will be implemented, redesigned according to the clinical practice and another completed trial [17]. If certain emergency situations occur, such as laryngeal spasm, an additional propofol (20–50 mg), methylprednisolone (40–80 mg, increasing the oxygen flow, gastroscope withdrawal, and positive pressure ventilation via the face mask, even rocuronium bromide 0.6 mg/kg and tracheal intubation if needed. No modification of randomized intervention (esketamine/saline); propofol dosing could be adjusted per clinical need (MOAA/S score).

**Fig. 2 Fig2:**
[figure not shown]
Airway management protocol

Please consider revising the sentence " And in the emergency case of laryngospasm, an additional propofol (20–50 mg)" for clarity and completeness. Thank you, I change it.

Other adverse events (AEs) Management: In the case of HR < 50 beats/min, an intravenous injection of atropine (0.3–0.5 mg) will be administered. If the HR drops when NBP also decreases (a MAP 20% lower than at baseline), an intravenous injection of ephedrine (6–10 mg) would be administered and repeated as needed. If the HR is normal or above the normal range but with low NBP (< 90/60 mmHg or a MAP 20% lower than at baseline), deoxyadrenaline (50 ug) would be administered and repeated as needed.

### Criteria for discontinuing or modifying allocated interventions {11b}

Intervention may be stopped or modified if a participant experiences severe hypoxemia or other intolerable side effects. Worsening of the underlying condition requires alternative treatment. Incorrect randomization, eligibility errors, interim analysis result-related problems, and new safety data from other studies prompting modification or cessation need to discontinue or modify.

All substantial protocol modifications (changes to eligibility criteria, primary outcomes, or safety procedures) will be submitted for IRB review and approval prior to implementation, version-controlled in the protocol document (with revision dates), and updated on ChiCTR within 7 working days of approval.

### Strategies to improve adherence to interventions {11c}

To ensure strict adherence to the intervention protocol, we will implement a comprehensive strategy consisting of three key components: (1) standardized training for all study personnel using visual aids to reinforce proper procedures; (2) rigorous monthly audits by the Data Monitoring Committee (DMC) to review drug administration logs, titration compliance, and emergency protocol adherence; (3) a recognition system providing incentives for researchers who successfully complete 10 consecutive cases in full compliance with the study protocol. These measures are designed to maintain consistency in intervention delivery throughout the trial duration.

